#### ***Step 2: Determination of user acceptance and adherence***

a) Feedback on user acceptance will be captured with a feedback questionnaire and a semi-structured interview in week 6.

Every test and the overall impression of the App will be rated on a 5-step scale and comprise:

- Overall impression
- User friendliness
- Effort needed
- Meaningfulness for PwMS
- Willingness to perform the test in the future

**A mean response of > 3 on a Likert Scale will be the minimal requirement for test selection.**

b) Adherence will be calculated as percentage of completed repetitions divided by the total number of scheduled repetitions for each test. **The minimal adherence required for test selection will be 80%.**

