| Study design: | 
This feasibility study is a prospective observational proof of concept study in patients with MS with a control group of healthy volunteers. Duration of the study will be 6 weeks per patient. This study is the first step to identify precise, well accepted and meaningful digital biomarkers for patients with multiple sclerosis as a first step towards validation in further studies. Digital biomarkers will be captured by patient's own smartphones (iOS and Android) and by an additional smartwatch (Fitbit Versa 2).
 
30 patients with MS and 30 age- and sex- matched healthy controls will be included. All participants will be instructed by a study nurse at the beginning of the study to assure that all patients and healthy controls will use the App and perform all tasks in a similar and correct way. Within the study all participants will perform all tests repeatedly over a time period of 5 weeks (every test twice a week resulting in 10 repetitive performances/test). In week number 6 they will perform all questionnaires and will have their semi-structured interview.
 
Technical reproducibility of the markers will be the main criterion for reliability (<math>ICC \geq 0.6</math>, <math>CV < 20</math>, s. outcomes) and meaningfulness will be assessed by capturing expert and patient opinion, the latter obtained by a feedback questionnaire and a semi-structured interview at the end of the study.
 
Technical features and reproducibility of the tests will be also assessed in a group of healthy controls. In an exploratory analysis potential differences between healthy controls and PwMS on a group level will be assessed.
 |

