### **4.2 Primary Objective**

The primary objective of this study is to identify digital biomarkers that are technically reliable and measurable, and perceived as user friendly and meaningful for patients with MS (PwMS).

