## **6. STUDY DESIGN**

### **6.1 General study design and justification of design**

This feasibility study is a prospective observational proof of concept study in patients with MS with a control group of healthy volunteers. Duration of the study will be 6 weeks per patient. This study is the first step to identify precise, well accepted and meaningful digital biomarkers for patients with multiple sclerosis as a first step towards validation in further studies. Digital biomarkers will be captured by patient's own smartphones (iOS and Android) and by an additional smartwatch (Fitbit Versa 2). The smartwatches will be given to all participants and will be handed over to them after the study end (market value CHF 210/smartwatch).

30 patients with MS and 30 age- and sex- matched healthy controls will be included. All participants will be instructed by a study nurse at the beginning of the study to assure that all patients and healthy controls will use the App and perform all tasks in a similar and correct way. Within the study all participants will perform all tests repeatedly over a time period of 5 weeks (every test twice a week resulting in 10 repetitive performances/test). In week number 6 they will perform all questionnaires and will have their semi-structured interview.

This feasibility study aims to select the most reliable and meaningful biomarkers out of over 20 candidate biomarkers developed by our team.

Ranking of test performance will be done for each of the digital biomarkers by:

- Intra Class Correlation of at least 0.6 if repeated 10 times within 6 weeks
- Coefficient of variation must be less than 20% if repeated 10 times within 6 weeks
- User acceptance as assessed by a feedback questionnaire and a semi-structured interview at the end of the study (>3 on a likert scale).

For detailed criteria of performance see Chapter 11. Statistical Methods, 11.4.2. Primary Analysis.

For the exploratory analysis (potential differences between healthy controls and PwMS on a group level and correlation with already established assessment tools in their respective domains) age- and sex matched healthy controls will be included who will follow an identical test schedule and also provide their feedback about the App.

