#### **11.4 Planned Analyses**

##### **11.4.1 Datasets to be analysed, analysis populations**

All subjects who completed the study will be included in the primary analysis (per protocol analysis). An additional "intention-to-test" analysis comprising all eligible subjects will be performed as a sensitivity analysis.

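### Step 2 does not say in which group the acceptance and adherence thresholds are calculated, and the default population of all completers includes the healthy controls although the objective concerns patients

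*Protocol*

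**What the plan says.** - **Objective.** Section 4.2 seeks biomarkers that are technically reliable and "perceived as user friendly and meaningful for patients with MS (PwMS").
- **Source of the rating.** The synopsis, under study design, says "meaningfulness will be assessed by capturing expert and patient opinion, the latter obtained by a feedback questionnaire" and an interview at the end of the study.
- **Population.** Section 11.4.1 states: "All subjects who completed the study will be included in the primary analysis (per protocol analysis"). The synopsis repeats this. Neither place restricts it to participants with MS.
- **Who takes part.** Section 6.1: "30 patients with MS and 30 age- and sex- matched healthy controls will be included". The same section adds, in a sentence about the exploratory analysis, that "age- and sex matched healthy controls will be included who will follow an identical test schedule and also provide their feedback about the App".
- **Acceptance rule.** Section 11.4.2, Step 2 lists five rated aspects, one of which is "Meaningfulness for PwMS", and then sets the rule: "A mean response of > 3 on a Likert Scale will be the minimal requirement for test selection".
- **Adherence rule.** "Adherence will be calculated as percentage of completed repetitions divided by the total number of scheduled repetitions for each test". The minimum is 80%. No group is named here either.
- **Consequence.** Under Step 3, only tests that meet both requirements, and at least one of the two reliability criteria, are ranked for the validation study.

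**The concern.** The objective and the synopsis ask what patients think. The rules that decide whether a test goes forward do not say that patients are the ones counted. The only population statement that governs the primary analysis covers patients and controls alike, so an analyst who follows 11.4.1 to the letter would average the two groups.

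The populations differ by design. Patients may have an EDSS up to 6.5, whereas controls must be able to walk without aid (section 7.1). A single mean over both can hide a test that patients rate poorly or skip, or can drop a test that patients value and controls do not. Acceptance is the third primary outcome, and both thresholds are pass/fail requirements for a validation study in MS.

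The compliance alert in 3.5.1 and 8.4 would not necessarily reveal a selectively skipped test. It works on the share of a day's challenges completed, and missing one of 7 or one of 11 leaves 6/7 = 86% or 10/11 = 91%, above the 75% trigger.

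**Working it through.** The protocol gives no figure to reproduce here: section 11.2 states that no formal sample size calculation was done, and no rating SD or expected group difference is given. The check is weighted-mean arithmetic, followed by an illustration on stated assumptions.

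**Inputs from the protocol.** 30 patients and 30 controls (6.1), an identical schedule (6.1, 8.2.1), drop-outs replaced (7.4, 11.5), thresholds of a mean above 3 and adherence of 80% (11.4.2).

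**1. Share of controls.** 30/(30+30) = 50%. If completers ranged over 24 to 30 patients and 27 to 30 controls (assumed), the share would run from 27/57 = 47% to 30/54 = 56%.

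**2. Acceptance.** The pooled mean is (P + C)/2, where P is the patient mean and C the control mean. It exceeds 3 when C > 6 − P. So P = 2.6 passes once C > 3.4. The patient mean that just reaches the threshold is 6 − C:

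| Control mean | Patient mean at threshold |
|---|---|
| 3.0 | 3.0 |
| 3.5 | 2.5 |
| 4.0 | 2.0 |
| 4.5 | 1.5 |

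**3. Adherence.** The pooled figure is at least 80% when control adherence is at least 160% minus patient adherence:

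| Control adherence | Patient adherence at threshold |
|---|---|
| 80% | 80% |
| 85% | 75% |
| 90% | 70% |
| 95% | 65% |
| 100% | 60% |

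**4. The reverse.** P = 3.4 and C = 2.5 give (3.4 + 2.5)/2 = 2.95, so the test fails although patients accept it. Patient adherence of 82% with controls at 76% gives 79%, which also fails.

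**5. Chance of passing the rating threshold (assumed means and SDs).** P(pass) = 1 − Φ((3 − mean)/(SD/√n)), with n = 60 pooled and n = 30 for patients only. The per-person SD is assumed to be 0.7 to 1.0.

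| True patient / control mean | Pooled mean | Pooled rule passes | Patients-only rule passes |
|---|---|---|---|
| 2.8 / 3.4 | 3.10 | 78% to 87% | 6% to 14% |
| 2.6 / 3.5 | 3.05 | 65% to 71% | 0.1% to 1.4% |
| 2.5 / 3.0 | 2.75 | 0.3% to 2.6% | at most 0.3% |

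For the first row with SD 1.0, the pooled calculation is 0.10/(1.0/√60) = 0.77, giving 78%. For patients only it is −0.20/(1.0/√30) = −1.10, giving 14%. The third row shows that pooling changes little when controls do not lift the average over 3.

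**The case against.** **Pooling is not stated.** A reader might infer that the plan has decided to average patients and controls. It has not. Being included in the primary analysis is compatible with analysis by group, and the contrast drawn in 11.4.1 is between completers and all eligible subjects. The synopsis ties the questionnaire to patient opinion, and 6.1 mentions control feedback in a sentence on the exploratory analysis. These points stand. They do not settle the matter, because the synopsis background speaks of testing meaningfulness in patients and controls together, and for adherence almost nothing points to a patients-only reading. Nor is the question merely deferred to a SAP: the protocol itself sets the population, the thresholds and the selection consequence.

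**Controls can judge most of the items.** A reader might infer that all control ratings are uninformative. Controls perform the same challenges, so they can rate overall impression, friendliness, effort and willingness from experience. Only meaningfulness for patients lies outside it.

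**The direction of bias is unknown.** A reader might infer that pooling favours passing, since controls may find the tests easier. The protocol has no figure to support that, and the error can go either way. The contrasts in the working come from assumed means.

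**Deleted challenges.** Under 10.1.1 the study nurse can remove a challenge with safety concerns from an individual schedule, so it need not count as missed. That softens the adherence concern. It could also raise the control share of a pooled figure: if a test were deleted for 10 of 30 patients (assumed), with 10 repetitions each, 200 patient and 300 control repetitions would remain. Patients at (0.80 × 500 − 0.95 × 300)/200 = 57.5% would then pass with controls at 95%.

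**Passing is not selection.** Step 3 adds ranking and a judgement of complementary value, and the interviews give further information. This is correct and limits the harm, but the thresholds still decide which tests are ranked at all.

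**Conclusion.** The point holds as a conflict over the population, not as a settled wrong calculation. Step 2 leaves the group unnamed, and the default in 11.4.1 is all completers. That default does not fit the objective in 4.2 or the role the synopsis gives to the questionnaire. Taken literally, it gives controls about half the weight in both scores, and a test could pass while patients fail it or fail while patients accept it.

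The threshold arithmetic rests only on the 30:30 split. How often a decision would change rests on assumed group means and SDs, and the effect is nil if the groups rate and adhere alike. The text does not support saying that controls will supply half of the ratings, that the thresholds are biased towards passing, or that a rejected test will be reported as accepted by patients. The point is worth correcting before analysis because it concerns a primary outcome and a pass/fail selection rule.

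**What to change.** In 11.4.2, Step 2, state that the mean response above 3 and the 80% adherence used for selection are both calculated in participants with MS. Report the same figures for healthy controls separately and descriptively. Do not count control ratings of meaningfulness for patients towards the threshold. Carry a matching sentence into 11.4.1 and the synopsis.

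This takes one or two sentences and no new data. The price is precision: the mean rating rests on about 30 rather than 60 raters, so with the same per-person SD its standard error grows by √(60/30) ≈ 1.4. It then describes the group the objective names.

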### ***Step 3: Test ranking and selection***

For each test domain (vision, cognition, dexterity, movement) all tests that fulfill the minimal requirements for reliability in either ICC or CV, as well as user acceptance and adherence, will be ranked according to their performance in steps 1 and 2. Based on this ranking, tests for each domain will be selected to be further analysed in the validation study. If more than one test meets the minimal requirements, multiple tests per domain can be selected, if the different tests are of complementary clinical value.

#### **11.4.3 Exploratory Analyses**

The following exploratory analyses will be performed:

a) Potential differences between healthy controls and PwMS on a group level will be analysed with appropriate statistical tests, depending on data category and distribution (e.g. Wilcoxon Signed Rank Test). Although the study is not designed to detect statistically significant differences, results may be used to inform test selection for the validation study.

b) For each domain, correlations with established tests (e.g. "Catch-a-cloud" vs. Nine-Hole-Peg test) will be analysed in order to inform test selection for the validation study

#### **11.4.4 Interim analyses**

No interim analysis is planned due to the short study period (6 weeks).

#### **11.4.5 Safety analysis**

A safety analysis will be performed based on the reported AE and SAE after completion. This analysis will be performed by the CTU Basel in collaboration with the Principal Investigators.

#### **11.4.6 Deviation(s) from the original statistical plan**

Deviations from the original statistical plan will be described and justified in the final report.

### **11.5 Handling of missing data and drop-outs**

Drop-outs will be replaced. Missing data will be handled by multiple imputation. A complete case analysis will be added as a sensitivity analysis.

## **12. QUALITY ASSURANCE AND CONTROL**

Written SOPs and Working Instructions for all relevant study processes will be generated for all relevant study related processes and will be available on site. All study personnel will be trained before performing any activity related to study conduct. The respective documentation will be stored.

### **12.1 Data handling and record keeping / archiving**

Trial Master File (TMF), Investigator Site File (ISF) and paper based participant related information will be archived in the University Hospital Basel.

All electronic records will be archived in a designated database at the University Hospital Basel.

#### **12.1.1 Case Report Forms**

Study data including demographic data will be obtained at V1,V2 and V3, coded and documented by CRF (paper version) and will thereafter be integrated in the eCRF provided by local CTU. Data obtained from paper based semi-structured interviews, will be entered by the study nurse.

#### **12.1.2 Specification of source documents**

Source data will be available at the study site and include all original documents relating to the study, as well as the medical treatment and medical history of the participants. Source data are considered to consist of demographic data, visit dates, participation in the study and Informed Consent Forms, randomisation number, SAEs and AEs, test data, data from questionnaires and structured interviews, and the medical records.

#### **12.1.3 Record keeping / archiving**

All study data will be archived for a minimum of 10 years after study termination or premature termination of the clinical trial. Data will be stored at RC2NB ([name]).

## **12.2 Data management**

### **12.2.1 Data Management System**

Study data including demographic data will be coded and documented by CRF (paper version) and will thereafter be integrated in the eCRF provided and stored by local CTU (secutrial). Data obtained from feedback questionnaires are integrated in the eCRF, data obtained from paper based semi-structured interviews will not be entered into eCRF and will be stored by the neuropsychologist of the team.

The DREAMS Application will collect sensor data from participants' smartphones while they are performing the activities. When a study subject completes a task on his or her

smartphone, the DREAMS App sends the compressed and encrypted raw data to the DREAMS cloud for validation and processing. Data from the participants' wearable (FitBit) is collected via that wearable via an API (interface) of the manufacturer (FitBit). Healios and FitBit have established an interface through which the data is transferred securely from FitBit to the central database. The data captured via the App is directly stored in a table structure that reflects the structure of the App and the activities. Each of the datasets is linked to the user via a coded patient identifier, along with time and date stamps.

The central database (DREAMS cloud) is a MySQL database management solution that is hosted in an Amazon WebServices (AWS) environment. During the study, the data is managed by Healios database administration. The DREAMS cloud is internally organized by a multitude of microservices in a "virtual private cloud" (VPC) hosted on a server farm by Amazon Web Services (AWS) in Frankfurt, Germany as primary zone. Dublin, Ireland is set-up as secondary zone with the objective of achieving high availability. The system architecture is divided into separate, independent microservices, to increase flexibility, scalability and reusability of codes. The DREAMS cloud includes an administrator service as a gateway, a queue service that controls asynchronous jobs in order to reduce the time of response of the system, a user data service to manage the user data, a manager service to manage transactional information related to the tests ("challenges"), e.g. schedule, completion, reporting, and a validator service that validates and parses the raw data and generates a new dataset, called "pre-processed" data. Finally, a processor service runs the different algorithms over the pre-processed data and will generate the processed data ("results", e.g. features/metrics). Each stage of the data (raw, pre-processed and processed/results) will be stored in a database called "Precard DB".

The DREAMS platform will send each dataset (raw, pre-processed and processed data) daily to a data warehouse hosted on local premises by University Hospital Basel IT department, where the data is mirrored.

#### **12.2.2 Data security, access and back-up**

The DREAMS Application is downloaded on the personal smartphone of study participants by a trained study nurse or physician who also assigns each participant a unique study code. Neither the DREAMS App nor the RC2NB main partner Healios GmbH have access to any personal (health) information of study participants. The lookup-table of study codes and patient IDs remains with RC2NB and is not accessible to other parties. The solution is hosted on a fully secured and encrypted virtual private network (VPN) Amazon WebServices (AWS) environment. To ensure high security standards, AWS functionalities are used, such as logically isolated virtual private networks, database encryption, user and authentication management, activity logging, DDoS protection as well as daily-encrypted backups. Data transmission between the App cloud and University Hospital IT and is encrypted via HTTPS with AWS Certificate Manager.

Access to data is limited to the designated data manager at Healios GmbH, and authorized study personnel who require the data to fulfil their duties within the scope of the research project

The servers are located in Frankfurt, Germany (primary) and Dublin, Ireland (secondary). All the databases have an integrated back-up system for regular backups. In addition, the DREAMS platform will send daily mirrors to a data warehouse hosted on local premises by University Hospital Basel IT department.

### **12.2.3 Analysis and archiving**

Data will be extracted from the data warehouse upon study completion and analysed by designated data analysts/biostatisticians at RC2NB and CTU Basel. Researchers from University of Basel (sciCORE) and 3rd party collaborators can also receive copies of pseudonymized data sets as foreseen in respective data sharing agreements in accordance with applicable data privacy legislation. Study data will be stored in a data warehouse hosted by University Hospital Basel IT department. All study data will be archived for a minimum of 10 years after study termination or premature termination of the clinical trial.

### **12.2.4 Electronic and central data validation**

Procedures are in place to monitor that sensor data are captured and stored accurately and completely during the study and data management procedures are in place. Validation and processing include outlier detection, imputation of missing values, noise reduction and data analysis to extract features/metrics. The solution has completeness and validation checks to support quality of the manually entered data, e.g. when completing validated scales.

## **12.3 Monitoring**

Monitoring visits by the CTU Basel will be performed prior to study start and once after study completion, see separate monitoring plan by CTU.

Source data will be accessible to monitors and questions will be answered during monitoring.

## **12.4 Audits and Inspections**

External Auditing is not planned for this study. However, if an external audit/inspection should be requested by a regulatory body study, documentation and source data will be made available to auditors/inspectors.

## **12.5 Confidentiality, Data Protection**

Protocol, full dataset, statistical code and algorithms will be accessible by the Principal Investigators, the statistical as well as the data management teams during and after the study.

Direct access to source documents will be permitted for purposes of monitoring, audits and inspections.

## **12.6 Storage of biological material and related health data**

No biological material is stored for this study.

### **13. PUBLICATION AND DISSEMINATION POLICY**

A scientific publication will be prepared by the PI's of this study and is planned for 2021. The protection of trade secrets regarding the Medical Device will be respected.

